#### Targeted outdoor residual spraying

K-Othrine Polyzone is a polymer enhanced suspension concentrate aqueous formulation which has low odour and high level of safety. The polymer technology used in this formulation protects the active ingredients from weather conditions, rainfall, and mechanical abruption and ensures they remain available on treated surfaces for up to 3 months, thereby reducing environmental contamination. The insecticide dosage is 25 mg/m^2^ and is applied by trained operators using a residual hand compression sprayer (Semco, Japan). The target spray areas are outer walls covered or partly covered (corridors, staircase, parking, lobby or any corner liable to become a resting spot for mosquitoes) in all floors. We exclude sections of wall close to power plugs, elevator buttons, walls covered with wall paper, oil-based painted walls, or tiles. Residents are requested to remove edible plants, hanging clothes, pet cages (e.g. cats, dogs and birds), and to cover aquaria during the day of the intervention. Parts of corridors with such objects are not sprayed. Based on our previous findings showing the residual bio-efficacy of K-Othrine® Polyzone for 16 weeks [17, 21], TORS is conducted every 4 months in all premises in al intervention areas.

To control the quality of TORS spraying, each spray pump is equipped with a control flow valve. The latter is a device that fits next to the nozzle and ensures that output remains constant as the pressure in the spray tank decreases. The spray pumps are washed after each use to avoid clotting of the insecticide in the nozzles. All spray cans are washed thoroughly, checked, and calibrated once a week. During spraying activities, a quality control officer observes the spraying procedure and technique. Pictures and video recorded randomly by the officer will be used for the quality control evaluation, future reference, or records. Training and evaluation of spray and calibration is provided to all operators every 2 months.

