#### Deployment of auto-dissemination devices

Auto-dissemination devices are black plastic containers that mimic breeding sites for female mosquitoes. ADDs use In2Mix powder that contain two active ingredients. The first is technical grade pyriproxyfen (PPF) at doses of 0.375 g per refill sachet. PPF is an insect growth regulator (IGR) that prevents mosquito larvae from developing into adults. The second active ingredient is spores of the insect specific fungus *Beauveria bassiana* GHA strain at 0.05 g per refill sachet. Adult female mosquitoes that visit the ADD pick up the In2Mix powder solution from the statically charged netting. The fungus slowly kills the mosquitoes, while the PPF is transferred by the mosquito to surrounding breeding sites (i.e. auto-dissemination), thereby reducing *Ae. aegypti* populations by decreasing the emergence of new adult mosquitoes [15].

The strategy for ADD deployment in these urban settings was adapted from In2Care standard recommendation (1 trap/400m^2^), based on results from our pilot study in Johor Bahru, Malaysia [21], and another study evaluating the vertical infestation of *Aedes* in high-rise building [22]. Smart deployment of ADDs only on floors with higher expected mosquito density was found to be sufficient to reduce the mosquito population in the whole building.

The exact number of ADDs and suitable location is determined at the start of the study (Additional file 2). ADDs are deployed at the same time as TORS and distributed over each floor as evenly as possible and placed according to the manufacturer’s recommendations in semi-indoor environment such as corridors, multipurpose halls, lobby, prayer hall, shops, and parking (i.e. shaded sites).

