### Monitoring quality of TORS and ADDs post-application

The quality control monitoring for ORS was conducted in 4 clusters using a susceptible laboratory strain mosquito, resistant laboratory strain mosquitoes, and a wild field strain mosquitoes of *Aedes aegypti*. To assess post-application quality of K-Othrine® Polyzone spray, wall deposit bioassays are conducted 48 h after spraying and repeated every 3 weeks for a period of 4 months [25]. Standard WHO bioassay cones are firmly positioned onto the TORS treated wall in a perpendicular position using masking tape. Ten adult female mosquitoes (sucrose-fed, 3–5 days old, non-blood fed) are introduced into the bioassay cone for 30 min through the aperture using a battery-operated aspirator, and then collected back and observed for 24 h mortality. Three biological replicates of 10 mosquitoes are prepared for laboratory and field strains of *Aedes aegypti*. Residual effect of K-Othrine® Polyzone is determined by evaluating the knock down time and mortality rate. Knock down is observed for 30 min at 1-min intervals. After exposure, the mosquitoes are aspirated out, transferred to paper cups, held at 27 ± 2 °C with 75 ± 10% relative humidity and sugar-fed. The mortality is recorded 24 h after testing. The level of resistance is evaluated using the WHO criteria [33].

To assess ADD quality post-application, the presence/absence and estimated quantities of mosquito larvae in the water inside the ADDs are recorded at each service. The water was collected from randomised ADD (3 ADDs) in study sites and tested using laboratory strain of *Aedes aegypti*. Every month, 250 ml water samples are taken from three randomly selected deployed ADDs that are positive for *Aedes* larvae and brought back to the laboratory to confirm the presence and activity of the pyriproxyfen larvicide. In each 250 ml ADD water sample, 25 third instar (L_3_) larvae from the IMR rearing colony of *Aedes aegypti* are added [33]. Emergence of mosquito adults is monitored every day until all larvae have emerged or died or all larvae from control emerge into adult. An emergence rate of adult mosquito less than 10% is indicative of adequate pyriproxyfen quality in the ADD water sample. The samples are collected at the same time as the Container Index sampling and are used for quality control of the ADD and as positive control for the auto-dissemination testing.

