To assess auto-dissemination efficacy of the ADDs, water samples of nearby containers are assessed for pyriproxyfen content. The *Aedes*-positive samples from natural containers collected for the CI (as explained above) are used to monitor larval development. Per 10 ml water sample collected, one susceptible strain larvae (L_3_, *Aedes aegypti*) is added to the water. Emergence of adults is monitored every day until all larvae have emerged or died. Significant reductions in adult mosquito emergence rates (i.e. high rates of larval/pupal mortality) in the intervention cluster samples compared to the control cluster samples is indicative of pyriproxyfen autodissemination from the ADDs.

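### Lower emergence in intervention than in control container water measures the effect of the IVM package, not pyriproxyfen autodissemination specifically

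*Protocol article*

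**What the plan says.** The protocol article, under Monitoring quality of TORS and ADDs post-application, describes a bioassay for auto-dissemination. Its stated aim is that "water samples of nearby containers are assessed for pyriproxyfen content". The samples are those already found positive for *Aedes* in the container survey: "positive samples from natural containers collected for the CI (as explained above) are used to monitor larval development". The indicator is a laboratory larva: "Per 10 ml water sample collected, one susceptible strain larvae" is added, and the sample is followed daily until all larvae have emerged or died.

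The reading rule is then fixed. A significant fall in emergence, with deaths of larvae and pupae taken together, "in the intervention cluster samples compared to the control cluster samples is indicative of pyriproxyfen autodissemination from the ADDs".

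Elsewhere the article says that intervention clusters receive TORS with deltamethrin, ADDs and community engagement together (Interventions), and that "ADDs are deployed at the same time as TORS" (Deployment of auto-dissemination devices). Routine control, including larviciding within 24 h of a reported case, continues in both arms, and its date, extent and place are recorded (Interventions).

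**The concern.** The rule names one cause, pyriproxyfen carried from the traps, but the comparison is between arms that differ by several components. A null of no pyriproxyfen transfer is not the same as a null of equal emergence from all causes, and only the second is tested by comparing the arms.

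At stake is a mechanistic statement. The Discussion gives the ADDs their own role, sustaining low mosquito density while the spray acts on adults, and looks ahead to scaling up. A significant result reported as autodissemination would credit one component with an effect that the design cannot separate from the others. The reverse error is also possible: real transfer could be hidden if larviciding is more frequent in control clusters.

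**Working it through.** The article gives no expected emergence rate, sample size or error rate for this bioassay, so there is no figure to reproduce. The check sets the sections side by side and asks what the contrast identifies.

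**Step 1: what differs between the arms.**

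| Source of larval or pupal death | Intervention | Control | Where stated |
|---|---|---|---|
| Pyriproxyfen from ADDs | possible | no ADDs | Deployment of auto-dissemination devices |
| Deltamethrin from TORS, every 4 months | possible | no TORS | Targeted outdoor residual spraying |
| Routine larviciding after a reported case | yes, depends on cases | yes, depends on cases | Interventions |

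No group receives ADDs without TORS or TORS without ADDs. The two also share locations: corridors, lobby and parking are listed for both.

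**Step 2: what the contrast estimates.** As a simplification, let the causes act independently and let background mortality be equal in the arms. Write p for the proportion of test larvae stopped by pyriproxyfen from ADDs, s for the proportion stopped by spray residue, and l1 and l0 for the proportions stopped by routine larvicide in intervention and control samples. The ratio of emergence, intervention to control, is

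R = (1 − p)(1 − s)(1 − l1) / (1 − l0).

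- If s = 0 and l1 = l0, then R = 1 − p, and the protocol's reading is correct.
- If p = 0 but s > 0 with l1 = l0, then R = 1 − s, which is below 1. With enough samples the rule is met with no transfer at all.
- If p = 0, s = 0 and l1 > l0, then R is again below 1.
- If p > 0, s = 0 and l1 < l0, then R exceeds 1 − p. Transfer is understated and may be missed. This is the likely direction if the IVM lowers incidence, since fewer cases trigger less larviciding.

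One ratio cannot yield p while s, l1 and l0 are unknown, and the article gives none of them.

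**Step 3: do the described controls separate the causes?** The only named assay control is water from the ADDs, used as a positive control. It can show that the assay responds to pyriproxyfen. It cannot show that nothing else lowered emergence. The control-cluster samples lack the whole package, not just the traps.

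**Step 4: does the sampling rule separate them?** Taking only *Aedes*-positive containers screens out water lethal to field larvae, but the indicator larvae are a susceptible strain. The article monitors pyrethroid resistance in field mosquitoes, so water that wild larvae tolerate could still kill the test larvae. The protection is partial.

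**Step 5: is there other information in the reading?** The rule groups larval and pupal deaths together. The article describes pyriproxyfen as a growth regulator that stops larvae becoming adults, so the stage at death bears on the cause. Daily monitoring makes it available.

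**The case against.** The strongest reply is that the wording is already cautious and the competing mechanism is undocumented. The rule asks for significant reductions and calls them indicative. A reader might infer that any excess death is treated as proof; the text does not say so.

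Nor does any section show deltamethrin reaching container water in a lethal amount. Spraying is confined to covered or partly covered walls, and the polymer is said to reduce environmental contamination. The request "and to cover aquaria during the day of the intervention" is a precaution for the day of spraying, not evidence of later residue. A reader might want a false-attribution rate, but it would depend entirely on an assumed share of contaminated containers, so none is offered here.

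A reader might also extend the point to the trap-water check: "An emergence rate of adult mosquito less than 10% is indicative of adequate pyriproxyfen quality in the ADD water sample". The documents do not support that. The check involves no comparison between arms and uses only traps holding live *Aedes* larvae. For a depleted trap to pass, more than 90% of the added larvae would have to fail in water where wild larvae live, and nothing shows that this happens.

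Finally, emergence is not among the listed outcomes, the objectives concern the combined strategy, and a condensed article may leave further assay detail to the full protocol.

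All of this limits the size of the point. It does not remove it: the article itself states the attribution, and the contrast to which it is attached cannot isolate the traps. Larviciding needs no assumption about spray run-off, since its dependence on reported cases is stated.

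**Conclusion.** The point holds in a limited form. The comparison of emergence between arms estimates the effect of the IVM package, against a background of larviciding that may differ by arm. A reduction is compatible with autodissemination but not specific to it. The amount of mortality from causes other than pyriproxyfen is not in the documents, so neither the size nor the net direction of the error can be given. The conclusion rests on the stated composition of the arms, not on any assumed level of contamination.

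It does not follow that autodissemination is absent, that spray residue is the likelier cause, or that the dengue incidence analysis is affected. The conclusion also does not depend on whether the chi-squared or Fisher comparison of emergence under Secondary outcome is meant for this bioassay, which the article leaves unclear. If the full protocol contains a separate measurement of pyriproxyfen, the point reduces to the wording of the rule. It is a minor, easily corrected matter of interpretation.

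**What to change.** 1. Reword the rule: lower emergence in intervention than in control samples is reported as the IVM package's effect on emergence, compatible with but not specific to pyriproxyfen autodissemination.
2. Use the daily monitoring to record and tabulate larval and pupal deaths separately by arm.
3. Use the routine-control records of date, extent and place to flag samples from places and dates with larviciding, or repeat the comparison without them as a sensitivity analysis.

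Two apparent shortcuts should be avoided. Omitting all TORS-sprayed places would remove most of the intervention arm, because spraying covers all intervention areas every 4 months. Replacing the susceptible strain with the resistant laboratory strain used in the wall bioassays is also unsafe, because nothing in the article shows that it responds to pyriproxyfen in the same way.

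The cost is a weaker mechanistic statement about the ADDs and slightly more recording.

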### Data management

Epidemiological data are extracted from the e-Dengue system by the staff of the Vector Borne Disease Sector, Disease Control Division, Ministry of Health Malaysia. Confirmed dengue patients are assigned a unique anonymous code. Entomological data are reported on paper-based forms and subsequently entered into an Excel file by data managers at IMR. A second data manager checks the accuracy of the Excel file by comparing the paper-based forms and data entered in the Excel file. Access to the data is password protected and restricted to authorized study investigators and data management staff.

Both epidemiological and entomological data are sent to the department of Biostatistics in Lyon-France on a monthly basis. Data are controlled for consistency by the team in Lyon. The list of inconsistent or erroneous values (i.e. data queries) is sent to the data managers in IMR for verification. A database in SAS software is prepared for final statistical analyses. A common identifier for clusters is used in order to link the entomological and epidemiological databases.

The original paper-based entomological forms are stored in secured locked cabinets at IMR. As for epidemiological data, access to the data is password protected and restricted to only authorized study investigators and data management staff. The anonymized databases sent to the service of Biostatistics of Hospices Civils de Lyon are stored in the study folder on a secured computer server. Only the biostatisticians in charge of the analyses have access to the data. A daily backup of the study folder is made automatically.

No human samples will be collected for, or held by, this study. Entomology specimens will be stored at IMR. This study will be carried out in compliance with the Malaysian Personal Data Protection Act 2010, stipulating full protection of an individual’s personal information.

All data, documents, the database, and the intervention procedure will be available for audits by regulatory and independent authorities appointed by funders or IMR.

### Plans to promote participant retention and complete follow-up

Our previous study showed that regular contacts between the study population and the field workers create public trust [21]. To maintain adherence to the interventions, a liaison officer assigned to each cluster contacts (via phone call or messaging) the building manager regularly to collect all complaints and feedback from the population. The pest control organisation in charge of TORS and ADDs deployment provides also regularly feed back to the CE team on any concerns faced in the field. These are discussed and taken into consideration in order to improve adherence to the intervention.

### Statistical methods

Statistical analysis will be performed using the statistical analysis software SAS® version 9.4. or higher. Missing data will be reported and their impact on the outcomes may be explored. No interim analyses are planned.

### Primary outcome

The primary endpoint is to measure the effectiveness of the IVM approach on dengue incidence. The mean of the cluster-level incidence rates will be compared between the control and intervention arms. In each cluster, the incidence rate will be estimated as the ratio of the number of dengue cases registered during the trial (starting from the first cycle of spraying and ending three months after the last spraying cycle), divided by the number of person-years. The number of inhabitants per cluster, as obtained for the sample size calculation, is checked and corrected if needed during the site visits for the purpose of calculation of incidence rates.

A negative binomial regression model will be used to compare the incidence between control and intervention clusters as a final value from the end of the first intervention cycle. This will yield the rate ratio and its 95% confidence interval, taking into account overdispersion. The response variable for this analysis will be the number of cases, and the logarithm of the person-years will be included as an offset. Stratification (low versus medium income) will be included as a covariate.

### Secondary outcome

The main secondary outcome will be the OI. The latter will be estimated over the baseline and intervention period in the 24 clusters selected for entomological monitoring. To quantify the effect of the interventions on the proportion of positive ovitraps, a modified ordinary least squares regression model using a robust standard error estimator will be implemented [21]. Using this model, the effect of the interventions will be quantified by the estimation of a difference of risk with its 95% confidence interval. This analysis will be carried out for both species overall and for each of the two species of mosquito separately.

Larval count per ovitrap (LI) will be estimated in the 24 clusters selected for entomological monitoring over the baseline and intervention period. A negative binomial regression will be used with the number of larvae as the response variable. The analysis will be adjusted by the baseline measurement of the outcome. Using this model, the effect of the interventions will be quantified by the estimation of a ratio of means with its 95% confidence interval. This analysis will be carried out for both species overall and for each of the two species of mosquito separately if possible.

The adult population will be estimated by counting the number of adult female *Aedes* mosquitoes collected with sticky ovitraps during the study. The total number of adult females will be divided by the number of sticky ovitraps used to obtain the mean number of adult females.

The emergence rate, defined as the proportion of larvae that emerge as adult mosquitoes, will be estimated in each arm and compared between the two arms using the chi-squared test or the Fisher exact test. This analysis will be carried out for both mosquito species combined and for each species separately.

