#### Entomological data

Entomological data for the assessment of secondary outcomes are collected in 12 clusters randomly selected from each arm (24 in total) and stratified by socio-economic status (medium versus low cost).

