### Monitoring *Aedes* population densities

The density of *Aedes aegypti* and *Ae. albopictus* populations will be monitored monthly throughout the study period using larval and adult collection methods in a sample of 12 clusters per arm. Larval surveys are carried out using a minimum of 40 ovitraps per cluster. Each ovitrap consists of a 250-ml cylindrical, black plastic container (7.5 cm diameter, 9.0 cm height, 300 ml volume) filled with tap water to a depth of 5.5 cm and is equipped with a removable oviposition paddle made from a thin strip of brown hardboard (10 cm × 2.5 cm × 0.3 cm). Larval surveys start 5 weeks before the start of the intervention to measure the baseline density. Ovitraps are positioned randomly in spaces with minimum human, physical, and environmental disturbance: (a) in the semi-indoor environment—defined as the area outside of the housing units but still sheltered by the roof (e.g. shared corridor and stairway), (b) in partially or totally shaded outdoor areas (e.g. near bushes, small plants, and temporary structures), and (c) indoor (under the sofa, dining table, sink, bed, working / study desk) only in the apartments of those who volunteer to have them.

To determine the OI, all ovitraps are collected once a week and replaced by new ones with fresh tap water and egg-free oviposition paddles. The collected ovitraps are brought back to the IMR laboratory (Kuala Lumpur) for further processing. Ovitrap contents and oviposition paddles are transferred into plastic containers and labelled with the name of the cluster and date of collection. Larvae emerged from the eggs laid in the ovitraps undergo species identification [30, 31] using a compound microscope (Nikon Eclipse® E100, Japan).

To determine the CI, a minimum of 20 suspected mosquito breeding containers within 50 m radius of the study cluster are examined once a month in each cluster. Larval samples from the positive containers are collected in a sample bottle and brought back for identification. The larvae are allowed to emerge into adults for morphological identification.

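### Baseline adjustment is stated for the larval count but not for the ovitrap index, the main secondary outcome, although the baseline is collected in the same 24 clusters

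*Protocol article*

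**What the plan says.** All of this stands in the protocol article.

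- Secondary outcome section, status of the OI: "The main secondary outcome will be the OI".
- Same section, period and clusters: "The latter will be estimated over the baseline and intervention period in the 24 clusters selected for entomological monitoring".
- Same section, model: "a modified ordinary least squares regression model using a robust standard error estimator will be implemented". A reference is cited for the method. The result is a risk difference with a 95% confidence interval, for both species together and for each one. No covariate is named.
- Same section, next paragraph, on the larval count per ovitrap, analysed by negative binomial regression: "The analysis will be adjusted by the baseline measurement of the outcome".
- Monitoring Aedes population densities section: "Larval surveys start 5 weeks before the start of the intervention to measure the baseline density", and "Larval surveys are carried out using a minimum of 40 ovitraps per cluster". Traps are collected weekly.
- Entomological data section: the data come from "12 clusters randomly selected from each arm", stratified by low- or medium-cost housing.
- Primary outcome section: the housing stratum is named as a covariate in the dengue incidence model.

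**The concern.** The OI and the larval count come from the same traps, clusters and baseline weeks. An analyst who follows the text would adjust the lesser outcome for its baseline and leave the main one unadjusted. The housing stratum, which governed the choice of the 24 clusters and enters the primary model, is not in the stated OI model either.

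With 12 clusters per arm, clusters that start with a high or low index can easily fall unevenly between the arms by chance. A covariate that predicts the follow-up index removes part of that noise. At stake is the precision of the main evidence for the secondary objective, the effect on Aedes density.

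**Working it through.** **1. The two paragraphs side by side**

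| Item | Ovitrap index | Larval count |
|---|---|---|
| Clusters | 24 | the same 24 |
| Period of estimation | baseline and intervention | baseline and intervention |
| Model | modified least squares, robust SE | negative binomial |
| Effect measure | risk difference | ratio of means |
| By species | yes | if possible |
| Baseline adjustment | not stated | stated |
| Housing stratum | not stated | not stated |

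The remark on the period of estimation stands in both paragraphs, and the larval paragraph still adds a separate sentence on adjustment. So that remark does not by itself specify adjustment.

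**2. Inputs**

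The protocol gives no power, intracluster correlation (ICC) or expected effect for the OI, so there is no figure of its own to reproduce.

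- From the protocol: 12 clusters per arm, 40 traps per cluster (the stated minimum), weekly collection, 5 baseline weeks.
- Assumed: OI 30% or 50%; ICC 0.02 to 0.10; correlation r between a cluster's underlying baseline and follow-up index of 0.3, 0.5 or 0.7; normal cluster effects; about 30 follow-up rounds.

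**3. Precision gained from the baseline**

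Cluster-level OI was simulated with no effect, 6000 runs per scenario. Least squares on arm and stratum was compared with the same model plus baseline OI. SE reduction = 1 − √(variance ratio).

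| r | Variance ratio | SE reduction |
|---|---|---|
| 0.3 | 0.96 to 0.98 | 1-2% |
| 0.5 | 0.79 to 0.86 | 7-11% |
| 0.7 | 0.55 to 0.66 | 19-26% |

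Both models contain the stratum, so these gains come from the baseline alone. The gain from the stratum was not quantified.

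Hand check at ICC 0.05:

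- Reliability of a baseline of 5 × 40 = 200 traps: 0.05/(0.05 + 0.95/200) = 0.913.
- Reliability of a follow-up of 30 × 40 = 1200 traps: 0.05/(0.05 + 0.95/1200) = 0.984.
- Cost of estimating one slope with 24 − 3 = 21 residual degrees of freedom: 1 + 1/(21 − 2) = 1.053.
- Variance ratio ≈ (1 − r² × 0.913 × 0.984) × 1.053, which is 0.967, 0.816 and 0.589 for r = 0.3, 0.5 and 0.7. The simulation gave 0.973-0.977, 0.816-0.822 and 0.584-0.585.

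The textbook reduction 1 − √(1 − r²), which is 5%, 13% and 29%, is too optimistic here. It ignores the noise in a short baseline and the cost of the slope.

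In absolute terms, at OI 50% and ICC 0.05, the sampling SD of the risk difference falls from 0.046 to 0.0455, 0.0418 and 0.0352. With t quantiles 2.080 (21 df) and 2.086 (20 df), the 95% half-width goes from 9.6 percentage points to 9.5, 8.7 and 7.3.

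**4. The variance estimator, conditional on how it is built**

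Type I error at nominal 5%, cluster-level analysis, 24 clusters:

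| Standard error and reference | Arm and stratum | Plus baseline OI |
|---|---|---|
| Uncorrected sandwich, normal | 7.7-9.0% | 8.9-9.7% |
| Corrected for degrees of freedom, normal | 5.8-6.9% | not run |
| Corrected, t | 4.7-5.4% | 4.9-5.8% |

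Monte Carlo error is about 0.6 points. In the unadjusted model the uncorrected SE averaged 0.90 to 0.93 of the true sampling SD. The rough expectation with three coefficients is √(21/24) = 0.935.

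**The case against.** The strongest reply is that silence is not a decision. The article is a condensed document, an analysis plan may exist, and the OI method is referred to a cited study that is not shown. Covariate lists, clustering level and small-sample corrections are commonly settled there. Nothing in the OI paragraph excludes the baseline, and estimating the index over both periods is compatible with using it.

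Much of this stands. The accurate statement is that adjustment is not stated, not that it is ruled out. What remains is the asymmetry inside one section: adjustment was thought worth stating for the lesser outcome and was left out for the main one.

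Three stronger readings are tempting, and the document supports none of them.

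- *The unadjusted estimate is biased or its interval under-covers.* Clusters were randomised and the entomology clusters were drawn at random within each arm. A valid standard error already reflects chance imbalance. Leaving out the baseline costs precision only, and leaving out a balanced stratum tends to widen the interval.
- *The robust standard error is too small.* That holds if traps are treated as independent (a simulated type I error of 22-92% under assumed cluster SDs and durations) or if an uncorrected cluster sandwich is used with a normal reference. The article commits to neither.
- *Twenty-four clusters are too few.* A standard correction with a t reference brings the error back to about 5%, and the protocol sets no OI power target that 24 clusters could miss.

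**Conclusion.** The point holds as one of precision and consistency. As written, the main secondary outcome has no stated adjustment for a baseline that is collected in the same clusters and used for the larval count, nor for the stratum by which those clusters were chosen. The likely loss is small if clusters keep little of their baseline ranking (1-2% of the standard error at r = 0.3). It is worth having at r = 0.5 (7-11%) and substantial at r = 0.7 (19-26%). The correlations, the ICC, the index level and the number of follow-up rounds are assumptions; the trial's own baseline data would narrow them.

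The variance point is a conditional addition. It matters somewhat more once a baseline covariate is added, because the uncorrected version then reaches about 9-10%. The dengue incidence analysis in 300 clusters is not touched.

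**What to change.** State in the OI analysis that each cluster's pre-intervention OI and its housing stratum enter the model as covariates, for both species together and for each species with its own baseline index. In the same sentence, say that the robust variance is clustered on locality, with a small-sample correction (for example CR2 with Satterthwaite degrees of freedom, or a degrees-of-freedom correction with t on clusters minus parameters) based on the 24 clusters.

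The change is wording only and needs no new data. The cost is one degree of freedom per covariate and slightly wider limits: a t quantile of about 2.09 with 20 degrees of freedom, against 1.96 from the normal. If r is near 0.3, the gain from the baseline will be negligible. The covariates should be fixed before the follow-up data are compared by arm.
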